### Statistical analysis

#### Aim 1

To develop the TAS test protocol and validate it against p-tau181, data from 350 participants with no cognitive impairment will develop the model. Data from the remaining 150 participants in this validation dataset will determine the model’s sensitivity and specificity in detecting preclinical AD. Replicates of plasma biomarkers will be assessed for outliers and then averaged. Hand-movement data will be summarised for each participant. Participants with unimpaired cognition and mean p-tau181 above a diagnostic cut off will be classified as ‘preclinical AD’. We will use multiple logistic regression to model the associations between movement features and p-tau181 positivity. Covariates may include age, sex, ApoE4 genotype, years of education, and handedness. As a secondary, more agnostic approach, we will use a deep learning approach to discover features in the video and keyboard movement data that map to p-tau181 positivity. To validate the TAS Test multivariable model, we will use cross-validation for model selection to avoid overfitting and bootstrap procedures to estimate model uncertainty. We will independently validate the model using the remaining 150 participants’ data. Receiver Operating Characteristic (ROC) curves will be plotted against the positive p-tau181 cut-off to assess the sensitivity and specificity of movement models to identify the preclinical AD stage. As TAS Test is intended as a screening test, the resulting curves will allow users to make informed choices about sensitivity and specificity that align with their research or health promotion goals.

#### Aim 2

To validate prospectively against cognitive decline, we will assess the sensitivity and specificity of TAS Test to predict cognitive trajectories (“stable” and “declining”) using ROC curve analysis. We will estimate 5-year cognitive decline/MCI/AD risk using baseline TAS Test data in a sub-sample of 300 people. Clinical diagnostic categories are: cognitively unimpaired, MCI, and AD. Covariates considered in the model will include age, sex, ApoE4, years of education, and handedness. We will use Bayesian multinomial logistic regression with regularizing priors to estimate the covariate adjusted log-odds of being in each diagnostic category at 5 years as predicted by baseline TAS Test results. The resulting prediction model will estimate posterior highest density intervals for 5-year risk of conversion to MCI and AD using TAS Test results. There is a risk that not all participants classified as MCI will have prodromal AD (as MCI is a heterogeneous group with a variety of causes) but to account for this, we will perform post-hoc analyses of sub-groups with indicators of higher risk, for example, amnestic sub-type of MCI, p-tau181 positive, ApoE4, longitudinal cognitive decline. Data analysis and statistics will be performed in consultation with a biostatistician.

*Descriptive statistics*: The quantitative variables will be described using mean, standard deviation (SD) and range, or median and inter-quartile range if not normally distributed; Qualitative variables will be described using frequency and percentages.

*Test-retest reliability* will be assessed between the first and second completions of TAS Test at home (12 months), and between completions in the research centre and the home (3–6 months). Stability of the TAS Test assessments will be analysed by measuring the intra-class correlation coefficient and by use of Cohen’s kappa coefficient of agreement.

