### Aims and hypotheses

The aims of the study are to:Develop and validate the optimal TAS Test protocol to detect preclinical AD and,Validate TAS Test to prospectively estimate 5-year risks of cognitive decline and AD.

We hypothesise that, for adults aged 50 years or older, TAS Test will:Detect preclinical AD (defined as positive blood p-tau181, normal cognition) with high sensitivity and specificity.Estimate the 5-year risk of accelerated cognitive decline and dementia with high precision.

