#### Participants

The participants will be recruited from the Tasmanian Healthy Brain Project (THBP) [31] at the University of Tasmania (UTAS) (ethics reference H0018265), and The Healthy Brain Ageing (HBA) Program [32] at the University of Sydney (protocol number 2019/271).

The THBP is a National Health and Medical Research Council (NHMRC)-funded, prospective cohort study that evaluates cognitive ageing in older adults who reside in Tasmania, Australia. Between 2010 and 2014, 556 participants aged 50 years and older were recruited (mean age 60 years) and underwent detailed neuropsychological and cognitive assessments, medical screening, and genetic tests at baseline, with detailed (4–6 hours) annual cognitive assessments for 4 years, then biennially.

The HBA is a specialist early intervention clinic and prospective cohort study that has recruited more than 1,000 participants aged 50 years and older (mean age 66 years) who have concerns about their cognition and reside in New South Wales, Australia. All receive detailed annual clinical phenotyping, including neuropsychological and medical assessments.

Participants from THBP and HBA will be invited to take part in the TAS Test study via email invitation or in person at a scheduled study visit. Inclusion criteria: Male and female adults ≥50 years old with unimpaired cognition. Exclusion criterion: Participants with impaired cognition, defined as declining cognitive trajectories measured by CANTAB Paired Associates Learning (PAL) total errors adjusted for age and sex, and a score > 1.5 SD above the mean total errors adjusted [33]. The rationale for excluding participants with impaired cognition is that, in this study, we aim to develop a test that discriminates participants with preclinical AD (unimpaired cognition and positive p-tau181) from those with healthy ageing (unimpaired cognition and negative p-tau181). Participants may withdraw from the study at any time and for any reason without any consequence to their ongoing participation in THBP or HBA. When an individual withdraws from the study, all the information collected to that point will be kept in the database for data analysis or withdrawal analysis.

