#### Participants

All eligible participants in The Island Study Linking Ageing and Neurodegenerative Disease (ISLAND) will be invited to take part in the TAS Test project. ISLAND is a 10-year public health initiative that launched in 2019 at the University of Tasmania (ethics reference H0018264). The project aims to recruit 20,000 people over 50 years of age who live in Tasmania, Australia by the end of 2022 and decrease their dementia risk; the detailed protocol is described in Bartlett et al. [43]. Nearly all assessments for the ISLAND project (except blood-based biomarkers that are collected in the research centre) are administered via an online portal where participants use a password to log in to their profile and complete a variety of assessments that are launched by the research team every few months. ISLAND participants complete extensive health questionnaires at baseline and will also be invited to complete TAS Test annually and CANTAB biennially, all online.

To date, over 13,500 participants have been recruited. CANTAB tests of cognitive function have been collected from approximately 3500 participants, TAS Test assessments from approximately 2200, and blood samples for the ApoE4 gene and blood biomarkers have been collected from approximately 2000. We can thus track cognition over time and identify people with scores indicative of cognitive decline as the sensitivity/specificity of CANTAB for classifying MCI and early dementia are 97/81% and 82/97% respectively [33].

The inclusion criteria for the TAS Test Aim 2 study are: ISLAND participants who have completed ≥2 TAS Test and ≥ 2 CANTAB tests. Exclusion criteria are: probable, or known, diagnosis of dementia or neurological disorders that impair hand function, speech or language function (e.g. stroke, Parkinson’s disease, collected through the baseline and interval ISLAND online health questionnaires). Participants will be classified as having ‘stable’ or ‘declining’ cognitive trajectories depending on PAL total errors at baseline (30 or more) and an increase of more than 10 total errors at follow-up assessments, as defined by Fowler et al. [44].

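### The Aim 2 cohort ROC names no age adjustment or demographic comparator, so it cannot show that TAS Test predicts decline beyond what age predicts

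*Protocol article*

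**What the plan says.** - **Hypothesis** (Aims and hypotheses): in adults aged 50 or older, TAS Test will "Estimate the 5-year risk of accelerated cognitive decline and dementia with high precision".
- **Cohort analysis** (Statistical analysis, Aim 2): "we will assess the sensitivity and specificity of TAS Test to predict cognitive trajectories", classed as stable or declining, by ROC analysis. The sentence names no covariate, stratum or comparator.
- **Reference standard** (Aim 2, Participants): people are classed as stable or declining "depending on PAL total errors at baseline (30 or more) and an increase of more than 10 total errors at follow-up assessments", following a cited study. No age or sex adjustment is stated.
- **Where covariates enter** (Statistical analysis, Aim 2): the next sentence turns to the clinic sub-sample, "We will estimate 5-year cognitive decline/MCI/AD risk using baseline TAS Test data in a sub-sample of 300 people". The covariate list comes after it: "Covariates considered in the model will include age, sex, ApoE4, years of education, and handedness". The Bayesian multinomial regression of diagnostic category is then described.
- **Age matching** (Aim 2, Participants): only the 100 controls of that sub-sample are matched on age and sex.
- **Contrast with Aim 1**: the exclusion rule there uses "declining cognitive trajectories measured by CANTAB Paired Associates Learning (PAL) total errors adjusted for age and sex". The Aim 1 sample size is set against a null model of age, sex, ApoE4 and education without finger tapping (AUC 0.75).

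**The concern.** A crude ROC asks whether TAS Test separates decliners from non-decliners by any route, and age is one such route. If older people make more PAL errors or gain errors faster, and also perform more slowly on TAS Test, some discrimination appears even if the test says nothing among people of the same age. The hypothesis speaks of accelerated decline, and the test is offered as a way to pick out high-risk people for prevention. For both purposes the useful question is what the test adds to age, which is known at no cost.

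The adjustment and matching that the plan does contain serve a different outcome (clinical diagnosis) in a different sample (the 300). The larger cohort analysis has no counterpart to the demographic null model of Aim 1, so a moderate AUC there would be hard to interpret.

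**Working it through.** **1. The age gradient in the plan's own projection.** Inputs from Sample size, Aim 2: 10,000 people, about 1300 aged 70–74 at 8.6%, and 700 aged 75+ at 16% (stated as more than 16%).

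0.086 × 1300 + 0.16 × 700 = 111.8 + 112.0 = 223.8, which agrees with the stated minimum of 200.

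The other 10,000 − 1300 − 700 = 8000 are under 70. Their rate is not given, so it is assumed. With c_i cases and k_i non-cases in age band i (youngest first), and C and K the totals, the AUC of age band alone, ties counted one half, is

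AUC = Σ c_i (Σ_{j<i} k_j + ½ k_i) / (C K).

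At 1% under 70, cases are 80, 111.8 and 112 (C = 303.8), and non-cases are 7920, 1188.2 and 588 (K = 9696.2):

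(80 × 3960 + 111.8 × 8514.1 + 112 × 9402.2) / (303.8 × 9696.2) = 0.788.

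For assumed rates of 0.5%, 2%, 3% and 5% the result is 0.85, 0.71, 0.66 and 0.59. The outcome here is dementia, not the PAL trajectory, so this shows only that the plan itself expects a clear age gradient.

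**2. A score that carries only age, with that gradient.** Assumptions: 2000 people in each five-year band from 50 to 69, 1300 at 70–74 and 700 at 75–84; risks of 0.54%, 1.08%, 2.15%, 4.3%, 8.6% and 16%; score = r × standardised age + noise; 200 simulated cohorts per setting.

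- Mean crude AUC for r = 0.2, 0.3, 0.4, 0.5: 0.558, 0.586, 0.616, 0.645.
- Age itself: about 0.775.
- The score with age removed: 0.50.

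**3. The PAL cuts simulated directly.** Assumptions: age about N(63, 8) limited to 50–90; baseline PAL errors with mean 15 at age 63 and SD 12; change with mean 1 at age 63 and SD 8; n = 400,000. Declining means 30 or more errors at baseline and a rise above 10, as the plan states. The score correlates 0.5 with age and carries nothing else. Selected rows:

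| Age slope of PAL level (errors/year) | Age slope of change (errors/year) | AUC of age | Crude AUC of score | AUC within one-year age strata |
|---|---|---|---|---|
| 0 | 0 | 0.502 | 0.498 | 0.497 |
| 0 | 0.2 | 0.597 | 0.549 | 0.500 |
| 0.3 | 0 | 0.593 | 0.550 | 0.502 |
| 0.8 | 0 | 0.716 | 0.607 | 0.498 |
| 0.5 | 0.2 | 0.717 | 0.613 | 0.502 |
| 0.8 | 0.4 | 0.822 | 0.670 | 0.498 |

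Wherever PAL depends on age, the crude AUC of the score is 0.55–0.67. Within age strata it is 0.496–0.506 in every setting. If the rise alone defined decline and change did not depend on age, age would have an AUC of 0.50.

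Only a correlation of 0.5 was run in step 3; weaker correlations give values nearer 0.50. The range 0.55–0.67 covers steps 2 and 3 together.

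**The case against.** **Silence is not a statement.** The article never calls the ROC unadjusted, and adjustment is often left to an analysis plan. What enters the ROC could also be a risk score that already contains age, since Aim 1 allows age as a covariate. This is fair, and the point is therefore put as what the analysis names. But the article does fix the outcome, the method and the place where covariates enter, and that place is the sub-sample model. If age is in the score, the increment over age still needs to be shown.

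**No success rule is set.** A reader might infer that any age-sensitive test would pass as validated because its interval would exclude 0.5. The documents do not support that: they set no such criterion for Aim 2. The only AUC benchmarks, 0.75 and above 0.90, belong to Aim 1 and another outcome. An AUC of 0.56–0.65 would hardly read as strong validation.

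**The size is assumed.** Step 2 uses dementia rates in place of PAL trajectories, and every TAS–age and PAL–age value is assumed. If PAL level and change were both unrelated to age, there would be no effect. The within-person rise is less exposed to age than the baseline cut. All of this stands.

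**Accelerated is not defined.** Reading it as faster than expected for age is an interpretation; a rise of more than 10 errors is a plausible definition too. Crude discrimination is also a legitimate measure for a population screen. Both stand, which is why the crude ROC should be kept.

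**Conclusion.** The point holds as a limit on what the cohort validation can conclude. As described, the Aim 2 ROC cannot separate prediction of decline from the tracking of age. Under the assumed values, an otherwise uninformative score correlated 0.2–0.5 with age has a crude AUC of about 0.55–0.67, against 0.50 once age is held fixed. The true size is unknown, and it is zero if PAL does not depend on age.

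A reader might go further and infer that the trajectory definition is wrong and must be replaced by an age-adjusted one. The documents do not support this. The cut-offs come from a cited reference standard, and changing them would require new cut-offs. The difference from the Aim 1 rule justifies a sensitivity analysis, not a replacement.

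**What to change.** In Statistical analysis, Aim 2:

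- Keep the crude ROC, labelled as a description of screening performance.
- Add either an age- and sex-adjusted ROC, or the AUC increment over a null model of age, sex and education (plus ApoE4 where available), on the pattern of the Aim 1 null model.
- Report sensitivity and specificity by age band, for example 50–59, 60–69 and 70+.
- Keep the cited trajectory definition as the reference standard. A version on age- and sex-adjusted PAL errors, as in the Aim 1 exclusion rule, can be a sensitivity analysis.

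Age, sex and education are already collected, so no new data are needed. ApoE4 depends on blood samples, which the article reports for about 2000 participants so far. The cost is in the results: the adjusted AUC or increment will probably look less favourable, and intervals within age bands will be wider.

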### Further data collected

Data will also be collected on age, sex, years of education, English as first language, dominant hand, motor and cognitive symptoms, levels of pain and anxiety, and neurological diagnoses (Supplementary file 1). The following passive data will be collected without user input: log in time, log out time, user’s real-time mouse track, click actions on website internet browser (Chrome/Firefox/Safari etc). By collecting times of start/stop button clicking, we can understand how participants behave when they are using the application. For example, if a participant clicks start and stop several times, this means that the recording process may be difficult for participants to use. Time of day may influence performance. The following system-related data will be collected: Internet Protocol Version 4 (IPV4) address, browser information (name, version, product, manufacturer, layout), operating system, computer screen resolution, webcam information (resolution and frame rate). By collecting system information, such as browser information (version, product, manufacturer, layout), operating system (version, platform), camera resolution, video upload time, we can evaluate how different system environments may affect application administration.

### Aim 2

To validate TAS Test to prospectively estimate 5-year risks of cognitive decline and AD.

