#### Design

We will undertake a prospective 5-year cohort study. We will invite 10,000 adults from a long-term cohort to complete online tests at home: (i) TAS Test every 12 months, and (ii) Cambridge Neuropsychological Test Automated Battery (CANTAB) [42] cognitive tests every 24 months. The prospective ‘high risk’ predictions of TAS Test will be validated against CANTAB, and clinically via in-person testing in a subsample of 300.

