### Sample size

#### Aim 1

We estimate that 17% (or 85 individuals) in the cognitively unimpaired THBP & HBA cohorts will have p-tau181 in the preclinical AD range [45]. We have performed ROC curve analysis using open data from Mollica et al. [19]. This showed area under ROC curve (AUC) of 0.75 for a null linear model including age, sex, ApoE4, and years of education, but not finger tapping, to detect p-tau181 positivity in CSF. To develop the multivariable model, power calculation showed the sample size to compare a screening test with an area under the curve (AUC) > 0.90 against the null model would require 60 positive p-tau181 cases and 290 controls. Thus, we will use 350 in the development dataset (expected 60 [17%] preclinical AD cases) and 150 in the validation dataset (expected 25 [17%] preclinical AD cases) to test cut-offs from the development model. The PROBAST tool [46] confirmed these combined development and validation strategies lower the risk of bias.

#### Aim 2

Based on the age distribution of ISLAND participants, we project that 8.6% of participants currently aged 70–74 years (a cohort of ~ 1300 from the 10,000 recruited) will develop dementia, and more than 16% of the 700 participants currently aged 75+ years will develop dementia over the study duration [47, 48]. Thus at least 200 participants will meet diagnostic criteria for dementia or MCI. Our sample size calculation aims to ensure precise estimation of model parameters while minimising potential of overfitting. A sample of 300 including 100 dementia cases would ensure accurate prediction of the outcome proportion (33%) with a targeted confidence interval of 28–38%. To target a mean absolute prediction error (MAPE) < 0.05, as recommended by Riley et al. [49], a sample of 300 would be adequate for up to 6 predictors in a parsimonious, statistically determined risk prediction model.

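### The clinical part of Aim 2 is called a validation of TAS Test's predictions, but it is sized and described as building a new risk model in the same 300 people

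*Protocol article*

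**What the plan says.** The Protocol article states the purpose under the Aim 2 heading: "To validate TAS Test to prospectively estimate 5-year risks of cognitive decline and AD". The Aim 2 Design paragraph says what is to be checked and where: the prospective high-risk "predictions of TAS Test will be validated against CANTAB, and clinically via in-person testing in a subsample of 300".

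The Aim 2 part of Statistical analysis then describes the clinical component. It starts from "We will estimate 5-year cognitive decline/MCI/AD risk using baseline TAS Test data in a sub-sample of 300 people". The method is "We will use Bayesian multinomial logistic regression with regularizing priors to estimate the covariate adjusted log-odds of being in each diagnostic category", and the output is described as follows: "The resulting prediction model will estimate posterior highest density intervals for 5-year risk of conversion to MCI and AD using TAS Test results". On adjustment it says "Covariates considered in the model will include age, sex, ApoE4, years of education, and handedness".

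The Aim 2 part of Sample size says that the calculation targets precise parameter estimates and limited overfitting. It concludes that 300 people "would be adequate for up to 6 predictors in a parsimonious, statistically determined risk prediction model".

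For Aim 1, by contrast, the same article gives a 350/150 development/validation split, cross-validation for model selection, bootstrap for model uncertainty, and this: "We will independently validate the model using the remaining 150 participants".

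**The concern.** To validate a prediction is to compare a rule that already exists with outcomes that played no part in forming it. The clinical analysis does something else: it estimates coefficients from the diagnoses of the 300 and reports the fitted model. If accuracy is then judged on those same 300, the result is apparent performance, which is optimistic.

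Regularising priors shrink coefficients, and posterior intervals express uncertainty given the model. Neither measures discrimination or calibration in people who were not used for fitting.

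At stake is the study's second headline conclusion, that TAS Test is validated to estimate 5-year risk. Once the 48-month outcomes have been linked, a rule can no longer be fixed in advance of them.

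**Working it through.** **1. The plan's own figures.** The stated inputs are n = 300, 100 cases (33%), an interval of 28–38%, and mean absolute prediction error (MAPE) below 0.05 with up to 6 predictors.

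- Interval, assuming 95% and the Wald form: 0.33 ± 1.96 × √(0.33 × 0.67 / 300) = 0.33 ± 0.053, or 27.7% to 38.3%. This agrees with the plan.
- MAPE, assuming the regression formula for a binary-outcome model (its coefficients are not printed in the article): ln(MAPE) = −0.508 − 0.544 ln(n) + 0.259 ln(φ) + 0.504 ln(P), with φ = 1/3 and P = 6. At n = 300 this gives 0.0502. Solving for MAPE = 0.05 gives n = 302, which agrees with 300 within rounding.

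Both figures reproduce. Both concern how well a model's parameters and predictions can be estimated when it is built. Neither sets the precision with which an existing rule's sensitivity, specificity, discrimination or calibration would be tested.

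**2. The passages side by side.**

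| Element | Aim 1 | Aim 2, the 300 |
|---|---|---|
| Stated purpose | Develop and validate | Validate |
| Sample size basis | 350 to develop, 150 to validate | Parameter precision, overfitting, number of predictors |
| Model fitted to | The 350 | The 300 |
| Out-of-sample check stated | Cross-validation and held-out 150 | None |
| Fixed score named as the thing tested | Cut-offs from the development model | None |

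**3. Room in the model.** Five covariates are listed for consideration. If all are kept at one term each, 6 − 5 = 1 predictor is left for TAS Test. A three-category outcome also needs two coefficients per predictor, so 6 predictors mean 12 slopes. TAS Test data must therefore be condensed or selected in some way, and the article does not say how for this model.

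**4. Illustrative size of the optimism.** These are simulations under assumptions that are not in the article: 300 people, 100 cases, a binary outcome, independent normal predictors, and ridge penalty 1 (equivalent to prior SD 1).

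| Setting | AUC in fitting data | AUC in new data | Gap |
|---|---|---|---|
| 6 fixed predictors, true AUC near 0.75 | 0.76 | 0.74 | about 0.02 |
| 6 fixed predictors, no signal | 0.58 | 0.50 | about 0.08 |
| Best 6 of 20, no signal | 0.63 | 0.50 | 0.13 |
| Best 6 of 100, no signal | 0.69 | 0.50 | 0.19 |

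A three-category version with equal categories, 6 fixed predictors and weak signal gives 0.66 against 0.62, a gap of about 0.04.

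**5. Would a split of the 300 help?** Holding out 90 leaves about 30 cases. At an assumed sensitivity of 0.80, the 95% half-width is 1.96 × √(0.8 × 0.2 / 30) = 0.14. With all 100 cases it is 1.96 × √(0.16 / 100) = 0.08. Resampling the full 300 is the better use of the data.

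**The case against.** Several counter-arguments have force.

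- **Detail may lie elsewhere.** A journal article condenses, and a full protocol or SAP may add resampling for Aim 2. This stands, so a reader should not infer that the model will never be tested. What remains is that the stated aim says validation while both the stated sample size basis and the stated analysis describe development. Added detail would have to change one or the other.
- **Aim 2 does contain a performance assessment.** The Aim 2 analysis opens with sensitivity, specificity and ROC curves for stable and declining CANTAB trajectories. This stands, and it would be wrong to infer that Aim 2 as a whole lacks one. But no fixed score or cut-off is named for it, and it does not address absolute 5-year MCI/AD risk.
- **The Aim 1 algorithm may be carried forward.** The Abstract's Methods can be read that way, since the classifier and the 5-year precision appear in one sentence, and the Design paragraph's high-risk predictions presuppose a rule. The link is ambiguous rather than absent. The Aim 2 analysis text does not make it.
- **Large AUC inflation is not shown.** Pure noise is the extreme case. The best-6-of-many rows assume screening of features in the 300, which the article does not describe. Entering dozens of features together would breach the plan's limit of six. The Discussion's figure of more than 10,000 data points belongs to the multivariable model, a term the article uses for Aim 1. No AUC is promised for the 300.
- **An Aim 1 rule is no simple remedy.** A model trained on p-tau181 positivity estimates biomarker status, so its calibration to a 5-year diagnosis has no meaning without recalibration. This stands and shapes the fix.

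**Conclusion.** The concern holds for the clinical component of Aim 2. The aim and design announce validation of existing predictions in the 300, while the sample size and analysis describe developing a new model on those 300. No pre-specified score is named and no out-of-sample assessment is stated. Followed as written, this component would not justify saying that 5-year MCI/AD risk estimation has been validated.

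A reader might go further and infer that the design makes validation impossible. The article does not support that, because the outcomes arise at 48 months and a rule can still be fixed before they are linked. That Aim 1 will finish in time is likely, since its last TAS Test is at 6 months, but this is an inference; no completion date is given.

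The size is conditional: about 0.02 in AUC with six fixed predictors and good signal, about 0.08 with none, and more if features are selected in the 300. These values rest on the simulation assumptions above. They show the range of same-data optimism and do not predict this study's results.

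**What to change.** 1. **Call the multinomial model in the 300 model development.** Report its discrimination and calibration with bootstrap optimism correction or cross-validation, repeating any feature selection or reduction within each resample. The 300 are drawn by 48-month CANTAB status (200 with scores suggesting impairment, 100 age- and sex-matched controls), so the diagnostic mix is set by sampling. Before giving absolute risks, account for this, for example by reweighting to the cohort with the known sampling fractions.

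2. **For the validation claim, fix a TAS Test score and high-risk cut-off in advance.** It could come from Aim 1. Record it before the 48-month CANTAB results and clinic diagnoses are linked to TAS Test data. Report its discrimination, sensitivity and specificity against CANTAB trajectory and against clinic diagnosis, using the same sampling weights for the latter. Do not claim that a probability trained on p-tau181 is calibrated to 5-year diagnosis unless it has been recalibrated and that step is itself assessed.

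3. **State in the Aim 2 text which analysis supports which claim.**

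The cost is revised wording and some extra computation, with no new data. Reported performance will probably look less favourable, and weighted estimates will be less precise.

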A sub-sample of 300 people will be selected from the main ‘TAS Test Aim 2’ cohort to attend the linked ISLAND Cognitive Clinic; this clinic provides facilities and expertise for gold standard clinical consensus diagnosis in a ‘one-stop’ interdisciplinary clinic where participants will have neuropsychological, and geriatrician or neurologist assessments, MRI brain scans, and ApoE4 tests. To select this cohort of 300 people for further face-to-face assessments from the larger cohort of up to 10,000 participants, we will invite 200 ISLAND participants (randomly selected) from those who have CANTAB scores (at the 48 month test point) indicative of MCI or AD – ie those with learning/working memory or attention cognitive deficits. A further 100 will be selected as age- and sex-matched controls from the Aim 2 participant cohort (using stratified random sampling) that comprises people with CANTAB scores indicative of unimpaired cognition.

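### In the 300-person Aim 2 model the MCI category mixes MCI already present at baseline with new MCI, yet the result is reported as risk of conversion

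*Protocol article*

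**What the plan says.** Entry to Aim 2 (Methods, Aim 2, Participants) is open to "ISLAND participants who have completed ≥2 TAS Test and ≥ 2 CANTAB tests". The exclusions are "probable, or known, diagnosis of dementia or neurological disorders that impair hand function, speech or language function". Neither MCI nor a low baseline CANTAB score is listed. Aim 1, by contrast, admits "Male and female adults ≥50 years old with unimpaired cognition" and gives a rule on the CANTAB Paired Associates Learning (PAL) test for excluding impaired people.

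For the clinic sub-sample of 300, the same Aim 2 section draws 200 at random "from those who have CANTAB scores (at the 48 month test point) indicative of MCI or AD", with no condition on the baseline score. It adds 100 age- and sex-matched controls whose CANTAB is in the unimpaired range. The Aim 2 Measurements section schedules CANTAB at baseline, 24 and 48 months.

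Under Statistical analysis, Aim 2, the sub-sample outcome is a clinical diagnosis in three groups: unimpaired, MCI and AD. A Bayesian multinomial model estimates the odds of each group at five years from baseline TAS Test. The named covariates are age, sex, ApoE4, education and handedness. The output is described as "5-year risk of conversion to MCI and AD using TAS Test results".

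A separate analysis in that section concerns stable or declining trajectories, classified "depending on PAL total errors at baseline (30 or more) and an increase of more than 10 total errors at follow-up assessments".

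**The concern.** Conversion is a change: someone free of the condition at the start has it at the end. The model describes a state at five years. The two agree only if everyone analysed was free of the condition at baseline, or if baseline status is conditioned on. For MCI the plan does neither.

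TAS Test includes memory, visuospatial, processing-speed and language tasks. A person with MCI on the day of the first TAS Test would be expected to score worse that day and to remain in an impaired category later. The association then reflects detection at baseline rather than foresight. Aim 2 exists to show prospective risk estimation, so this bears directly on what may be concluded about MCI.

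**Working it through.** **1. The plan's own figures.** The plan gives no baseline MCI prevalence, so there is no stated figure for this mixture to reproduce. The nearby sample-size figures do reproduce:
- 100 dementia cases in 300 gives 0.333 ± 1.96 × √(0.333 × 0.667 / 300) = 28.0% to 38.7%, against a stated 28–38%.
- Projected dementia cases are 0.086 × 1300 + 0.16 × 700 = 111.8 + 112.0 = 223.8, consistent with at least 200.

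These neither cause nor remove the problem.

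**2. Tracing one participant.** Take someone with MCI at baseline and unchanged MCI at five years.
- Entry: not excluded, because only dementia and certain neurological disorders are.
- Selection: eligible for the 200 on the month-48 CANTAB.
- Outcome: MCI at the consensus diagnosis.
- Model: no term records the baseline state.
- Report: contributes to the risk of conversion to MCI.

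**3. How many could be affected.** The sample-size section plans 100 dementia cases in the 300. If all 200 impaired invitees are confirmed as impaired, 200 − 100 = 100 are left with MCI. On the plan's numbers, then, at most about half of the 200 could be unchanged baseline MCI. Let f be the prevalent share of that MCI group; the documents do not give f.

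**4. Effect on discrimination.** Against a common set of unimpaired controls this identity is exact:

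apparent AUC = f × AUC(prevalent MCI) + (1 − f) × AUC(new MCI)

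With assumed AUCs:

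| f | 0.85 prevalent, 0.65 new | 0.80 prevalent, 0.60 new |
|---|---|---|
| 0% | 0.65 | 0.60 |
| 10% | 0.67 | 0.62 |
| 25% | 0.70 | 0.65 |
| 50% | 0.75 | 0.70 |
| 75% | 0.80 | 0.75 |

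The apparent AUC exceeds the true one for conversion only if TAS Test separates prevalent MCI better than new MCI. That is likely for a test with cognitive content, but it is not established.

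**5. What a baseline CANTAB restriction would do.** The Aim 2 Participants section gives CANTAB sensitivity and specificity for MCI as 97% and 81%. Applied at baseline to the 100 MCI cases of step 3:

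| f | New MCI kept (0.81 × new) | Prevalent MCI missed (0.03 × prevalent) | Remaining prevalent share |
|---|---|---|---|
| 10% | 0.81 × 90 = 72.9 | 0.03 × 10 = 0.3 | 0.3 / 73.2 = 0.4% |
| 25% | 0.81 × 75 = 60.75 | 0.03 × 25 = 0.75 | 0.75 / 61.5 = 1.2% |
| 50% | 0.81 × 50 = 40.5 | 0.03 × 50 = 1.5 | 1.5 / 42.0 = 3.6% |

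The restriction nearly removes the mixture but costs cases. It may cost more than shown, since future converters could score worse at baseline than other unimpaired people.

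**6. Predictor count.** Five named covariates plus one TAS Test score, one parameter each, make six, which is the limit stated in the sample-size section. Baseline PAL would be a seventh.

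**The case against.** The strongest reply is that the exposure is narrow, and most of that reply stands.

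- Known or probable dementia is excluded at entry, so a later AD diagnosis is genuine conversion to AD, even from baseline MCI.
- The declining label requires a rise of more than 10 PAL errors, so an unchanged person does not meet it. That definition also uses baseline PAL errors, which is a separate question.
- The month-48 CANTAB only selects invitees; the outcome is the clinical diagnosis. The model itself is correctly described as giving a state at five years. The fault lies in the label and in the missing at-risk set.

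A reader might go further in three ways, none of which the documents support.

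- That a third to three quarters of the reported converters were impaired all along. Prevalence / (prevalence + incidence × (1 − prevalence)) gives 34% at 5% prevalence and 10% incidence, and 78% at 15% and 5%. Both rates are assumed, and the formula ignores reversion and the 100 planned dementia cases.
- That the size of the upward bias, or even its presence, has been shown. It is expected, not demonstrated. Nor does the level of risk follow, because the impaired fraction in the sub-sample is set mainly by the 200:100 design.
- That the 200 should be drawn only from people unimpaired at baseline. This would remove people in the MCI stage that precedes dementia and could endanger the 100 dementia cases.

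It may also be said that the covariate list is not closed and that such detail belongs in an analysis plan. But the article itself fixes eligibility, selection, outcome and label, and together these count unchanged MCI as conversion. The post-hoc sub-groups address whether MCI is prodromal AD; they do not restrict the main analysis to people unimpaired at baseline.

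**Conclusion.** The point holds for the MCI category of the 300-person model. Followed as written, the plan reports MCI that was present at baseline as conversion to MCI, and it is expected to credit TAS Test with foresight for what was concurrent detection. The size cannot be fixed from the documents. The AUC gains in the working, 0.05 at f = 25% and 0.10 at f = 50%, rest on assumed AUCs and assumed prevalent shares. Conversion to AD and the trajectory endpoint are not affected in this way. It should be corrected, because it changes what Aim 2 can conclude about MCI and the remedy uses data already scheduled for collection.

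**What to change.** Keep the sampling frame for the 300 and change the analysis and the wording:

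1. Estimate conversion to MCI only among sub-sample members whose baseline CANTAB was in the unimpaired range, with the cut stated in advance.
2. Report members impaired at baseline separately, as concurrent detection of MCI or as progression from MCI to AD.
3. For any analysis that pools the two, call the result the risk of being in the category at five years, and add a sensitivity analysis adjusted for baseline PAL.
4. State how members without a baseline CANTAB are handled, since entry requires two CANTAB tests but does not say that one must be the baseline test.

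The costs are fewer MCI cases and wider intervals for conversion. At 81% specificity, about 19% of truly unimpaired people would be misclassified by the baseline cut and lost from the conversion estimate. The adjusted sensitivity model would use seven predictors against the stated six, so either another covariate is dropped or the plan says that it relies on the regularizing priors.
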